### Data analysis plan

Efficacy outcomes will be determined using Cox regressions analyses, non-parametric regression analyses and survival analyses of the cohort of patients that fulfilled entry criteria but not exclusion criteria. A per-protocol and intention-to-treat analysis will be done. Final analysis will include a description of included participants, proportions of AEs and any serious AEs, the proportion of participants withdrawn or lost to follow-up, the cumulative success and failure rates by day 28 and day 60. Categorical variables will be compared using the χ^2^ test or Fisher’s exact test and continuous variables using quantile regression. The final data analysis will be performed when a total number of 88 outcome events have occurred. An interim analysis will be performed after 44 outcome events.

### Patient and public involvement

No patient or patient organisation was involved in design, recruitment or management of the study.

## Ethics and dissemination

The trial has been registered with ClinicalTrials.gov, and sponsor protocol number CP03. The investigational product is a blood product (not classified as a drug) and the regulatory agency is the National Inspection Authority for Health and Care, which has approved the trial. The trial has been approved by the National Ethical Review Agency (decision 2020-06277). Patients will be informed of the study verbally and in writing. Details about the trial including risks and benefits will be explained and any questions answered, including the information that all participants in the study are covered by the regular patient injury insurance. A copy of the written consent form will then be signed. If an amendment substantially alters the study design, or increases the potential risk to the patients, written informed consent must be obtained again for currently enrolled patients and must be provided to additional patients prior to their entry into the study.

The trial will be conducted in compliance with the ICH (The International Council for Harmonisation of technical requirements for pharmaceuticals for human use) guidelines for Good Clinical Practice, the latest edition of the Declaration of Helsinki and any local regulations.

On inclusion, an entry will be made in the patient’s medical record specifying that the subject is participating in this study, if CP treatment is given and that written informed consent has been obtained. Any apparent side effects experienced by the subject will be assessed from the time the subject signs the informed consent and as long as the subject is part of the study, and will be reported by study site personnel either as a baseline event or an AE. The study personnel will document any baseline events or AEs in the electronic case record form (eCRF), whether observed by the investigator or reported by the subject. The safety of the different treatment arms will be assessed with regard to AEs, baseline medical conditions and findings from the physical examination and laboratory tests. All AEs, irrespective of nature, will be followed until resolution or until end of the follow-up period.

The reporting period for AEs starts at inclusion and ends at the final follow-up visit 2 months after inclusion. Interim analyses will be done after inclusion of 100, 300 and 600 patients. The study will be stopped if a 30% difference in treatment outcome is detected and an independent data monitoring committee will be convened to review the data and determine if the study should be stopped or not. An external party will monitor the study regularly and ensure that the study follows Good Clinical Practice. Audits or inspections will be performed at the study site during or after the study. These visits may include source data verification and confidentiality documents are therefore created.

After completion of the study, a clinical study report will be prepared that will form the basis for a manuscript intended for publication in a medical journal. Data will only be reported in aggregated form, without being able to be attributed to an individual. Records of the study will be kept for 10 years after final signing of the clinical study report. Data will be entered into a database by the investigators at the coordinating hospital (Danderyd Hospital). Study ID will only be used on computerised records. The key will be stored with the case record forms (CRFs) at Danderyd Hospital. Only the sponsor, principal investigator and participating researchers will have access to all data. Source data comprising electronic medical records will be stored at each study site.

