### Sample size

Available data indicate that CP is safe and that high-titre CP can reduce mortality by approximately 30%. For that reason, a 2:1 randomisation is preferred. Randomisation will be done by computer-generated random numbers. Based on the available data, we assume 85%–88% survival in the control arm. Assuming a power of 80% and an alpha of 0.05%, 920 patients need to be enrolled.

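### The only stated stopping trigger is a 30% difference with no evidence threshold, and the same sentence both orders stopping and leaves it to a committee

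*Protocol article*

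**What the plan says.** Two places in the protocol article bear on early stopping.

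- Ethics and dissemination sets the looks by patient count: "Interim analyses will be done after inclusion of 100, 300 and 600 patients". The next sentence gives the rule: "The study will be stopped if a 30% difference in treatment outcome is detected". It then continues that an "independent data monitoring committee will be convened to review the data and determine if the study should be stopped or not". It states no test, confidence limit, spending function, minimum number of deaths, scale or direction.
- The Data analysis plan has an event-based schedule: "An interim analysis will be performed after 44 outcome events", and "The final data analysis will be performed when a total number of 88 outcome events have occurred". It attaches no stopping criterion to the interim look.

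The 30% is also the design effect. The Abstract, the strengths and limitations list and Sample size all use it for the expected reduction in mortality. For the comparator, Sample size says "we assume 85%–88% survival in the control arm", that is, 12–15% mortality.

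**The concern.** A trigger set equal to the planned effect, and judged on the point estimate alone, takes no account of how little information an early look holds. At 100 patients with 12–15% mortality, only about 12–15 deaths are expected if plasma does nothing, and an observed 30% relative difference is then ordinary chance variation. Even if plasma works exactly as planned, the estimate lies beyond the trigger about half the time at any look.

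The sentence also gives two incompatible instructions: its first half stops the study, and its second half asks a committee whether to stop. A reader cannot tell whether the 30% is binding or a prompt for review. At stake is whether a mortality trial ends on evidence that can support a conclusion.

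**Working it through.** **Plan's own figures.** The article states no operating characteristics for the stopping rule, so there is nothing to reproduce directly. The 88 events can be reproduced: with 920 patients, 2:1 allocation, 12% control mortality and a relative risk of 0.70, expected deaths are 920/3 × 0.12 + 2 × 920/3 × 0.084 = 36.8 + 51.5 = 88.3. This supports reading the 30% as relative. So does the control mortality: a benefit of 30 percentage points cannot arise in truth from 12–15%.

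**Inputs.** Control mortality 12% and 15% (Sample size); 2:1 allocation (Intervention); looks at 100, 300 and 600 patients, taken as 33/67, 100/200 and 200/400 control/plasma (Ethics and dissemination). Assumptions: trigger = observed relative risk ≤ 0.70; benefit direction only; day-28 status known for everyone at each look. Nominal significance means pooled z ≥ 1.96 in favour of plasma.

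**Step 1: evidence at the threshold.** With control risk p, plasma risk 0.7p and pooled risk p̄, z = 0.3p / √[p̄(1 − p̄)(1/n_c + 1/n_t)]. For p = 0.12 at 300 patients, p̄ = (100 × 0.12 + 200 × 0.084)/300 = 0.096. Then z = 0.036 / √[0.096 × 0.904 × (1/100 + 1/200)] = 1.00, two-sided p = 0.32.

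| Patients | Two-sided p at observed relative risk 0.70 (12% / 15% mortality) |
|---|---|
| 100 | 0.57 / 0.51 |
| 300 | 0.32 / 0.26 |
| 600 | 0.16 / 0.11 |

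**Step 2: crossing for benefit when plasma has no effect** (400,000 simulated trials).

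| | 12% mortality | 15% mortality |
|---|---|---|
| P(crossed) at 100, 300, 600, each look alone | 26.2%, 13.6%, 5.9% | 23.1%, 10.6%, 3.8% |
| First crossing at 100, 300, 600 | 26.2%, 5.1%, 1.3% | 23.1%, 4.0%, 0.9% |
| Any crossing | 32.5% | 28.0% |
| Share of crossings nominally significant | 1 − 0.878 = 12% | 1 − 0.853 = 15% |

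**Step 3: the same rule when the true relative risk is 0.70.**

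| | 12% mortality | 15% mortality |
|---|---|---|
| Crossed at 100 patients | 50% | 50% |
| Any crossing | 73% | 73% |
| Share of crossings nominally significant | 1 − 0.798 = 20% | 1 − 0.744 = 26% |
| Median observed relative risk at crossing | 0.49 | 0.55 |

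So if the trigger binds, 0.733 × 0.798 = 58% (12% mortality) or 0.733 × 0.744 = 55% (15%) of trials of an effective treatment stop early without nominal significance.

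**Step 4: false claim of benefit if the trigger binds.** With a two-sided 0.05 test at the stop, or at 920 patients if there is no stop, a significant result favouring plasma under no effect occurs in about 4.3% (12%) to 4.7% (15%) of trials, against 2.5%.

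**Sensitivity.** Counting a 30% difference in either direction, 68–75% of null trials cross. Read as 30 percentage points, the trigger is crossed in about 0%. Applied at the single 44-event look as an observed hazard ratio ≤ 0.70, z = √(44 × 1/3 × 2/3) × |ln 0.70| = 3.127 × 0.357 = 1.12, so 13% of null trials cross. Strict inequality, or a 34/66 split at the first look, moves the three-look figures by less than one point.

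**The case against.** The strongest reply is that the rule is not automatic. The sentence goes on to give the decision to an independent committee, so the 30% may only prompt a review. A reader might infer from Step 2 that 28–33% of null trials would be falsely stopped. The document does not support that: the figure is a crossing rate, and it equals a false-stop rate only if the trigger binds. What survives is that the sentence says both things, and on the advisory reading the committee is given no other criterion.

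A reader might also take 28–33% as the type I error. It is not. Most null crossings are not significant, and the false-positive rate for benefit in Step 4 is 4.3–4.7%. That is inflated, but the larger damage is inconclusive stopping.

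A third inference is that the sponsor's team must compare the arms in order to know when to call the committee. The wording allows this, but the article does not say who runs the interim analyses. Its sentence on who may see all data stands among record-keeping provisions for after study completion, so it is not evidence about interim access.

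Finally, a statistical analysis plan or committee charter not shown here may hold a proper boundary. Leaving such detail out of an article is no fault. But the article does state a rule, and a boundary elsewhere would conflict with it until the sentence is changed.

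**Conclusion.** The point holds as a badly fixed rule. The one stated trigger equals the design effect, carries no evidence threshold, and is first applied at about 12–15 expected deaths. Chance alone crosses it for benefit in about 28–33% of null trials, usually without nominal significance.

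If it binds, the consequence is mainly early, inconclusive stopping, an exaggerated estimate and lost power, with a smaller inflation of the false-positive rate. If it is advisory, the committee's only stated criterion is one that noise often meets.

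These sizes rest on the relative reading, which the document supports well; on benefit direction only; on "detected" in the rule meaning merely observed; on the patient-based looks; and on complete day-28 outcomes at each look. The looks are timed by inclusion, so some outcomes may be pending; fewer deaths would make the observed ratio noisier. The contradiction within the sentence depends on none of these assumptions.

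**What to change.** 1. Reconcile the two schedules first: looks at 100, 300 and 600 patients in Ethics and dissemination, against 44 and 88 events in the Data analysis plan. The information fractions depend on which one stands.
2. Replace the 30% trigger with a group-sequential boundary on the day-28 mortality test, for example Lan-DeMets O'Brien-Fleming spending, and state the spending convention. Adding an unadjusted two-sided p < 0.05 to the present trigger would not be enough: false stops for benefit would still be about 6.5–6.7% against 2.5%.
3. Constitute the independent committee before the first look, and word its output as a recommendation, so that the sentence no longer also orders a stop.

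The cost is a few sentences of protocol text, since the looks and the committee are already planned. The statistical price is a final test slightly below 0.05. For looks at 100, 300 and 600 with a final at 920 patients, it is about 0.044 if a single two-sided 0.05 is spent and about 0.047 if 0.025 is spent per side. These levels are illustrative and must be recomputed once the schedule is settled.
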